## Abstract

**Introduction:**

Cognitive impairment (CI) is a growing public health problem. Our study is based on the fact that cognitive assessment in community pharmacy focused on early identification of undiagnosed CI has received limited attention. As pharmacists are the most accessible health professionals due to the availability of community pharmacies to the public, they have the potential to bring improvement in this area. Early identification of at-risk patients with CI by performing cognitive testing within advanced pharmaceutical care may improve the availability of targeted physician-indicated treatment.

**Methods and analysis:**

The study is a multicentric study that will include cognitive screening within pharmaceutical care. We will use the Slovak version of the short form of the Montreal Cognitive Assessment (s-MoCA) test. Study participants will be at-risk patients undergoing cognitive screening in community pharmacies. Secondarily, we will evaluate the risk factors related to CI, such as at-risk medication use and modifiable dementia risk factors (e.g., cardiovascular and mental comorbidities, aging, and lifestyle habits).

**Ethics and dissemination:**

This study was approved by the Ethics Committee of the Faculty of Pharmacy, Comenius University Bratislava (Ethics Committee Statement 01/2024). All procedures follow the relevant guidelines and regulations and the Declaration of Helsinki.

## Introduction

1

### Epidemiology and cognitive screening

1.1

Cognitive disorders represent a growing public health concern given the increasing number of seniors reaching an at-risk age (1, 2), associated with a subjectively or objectively measurable decline in at least one of the domains of cognitive functions, such as verbal abilities, spatial orientation, episodic memory, processing speed and executive functions (3). Only limited attention has been given to cognitive assessment in the community pharmacy targeting the early identification of undiagnosed cognitive impairment (CI) (4–9). As pharmacists are the most accessible health professionals due to the availability of community pharmacies to the public, they have the potential to be involved in early identification of at-risk patients who have not yet received a professional examination by a physician (4). Dementia and Alzheimer’s disease are the most common cognitive disorders affecting older people aged 60+ (1, 10), with a globally devastating impact on society with a disproportionate burden on health, economic and social care (11–13). Therefore, prevention, diagnosis, and pharmacological and non-pharmacological treatment of dementia are among the international priorities of the World Health Organization (WHO) (1, 2). It is essential to recognize CI at a reversible stage, and early intervention and appropriate interventions can prevent the development of dementia. This stage called mild cognitive impairment (MCI), is a transitional phase between cognitive ability decline due to age and the terminal stage of CI, dementia. Mental health and memory problems are crucial issues with significant impact on life quality. They can also affect patients’ level of medication adherence and self-care ability, which can result in poor long-term health outcomes (5, 8). Secondarily, cognitive decline may also be accelerated by the use of at-risk medications, especially when taking them for a long time (14, 15). These drugs suppress the cholinergic neurotransmitter pathways affecting brain structures such as the hippocampus and the neocortex, which are already vulnerable to age-related CI (16). Analysis of chronic pharmacotherapy can help identify at-risk medications and suggest a safe alternative, if possible. Anticholinergics, sedatives and benzodiazepines are the commonly used drugs with adverse effects on cognitive function (15–18). When they are combined, their adverse effect is cumulative (15, 19). A well-used tool is an assessment of the anticholinergic burden (ACB) scale (17). Implementing cognitive screening for early identification of patients with CI into pharmaceutical care can forward these patients to a doctor without undue delay and allow early initiation of their treatment and monitoring of further cognitive deterioration. Moreover, treatment of CI could reduce the risk of non-adherence to pharmacotherapy for already diagnosed chronic diseases (5, 20). Community pharmacists are suitable for preventing dementia by implementing cognitive screening within advanced pharmaceutical care (5, 20). Early identification of at-risk patients with CI could improve the availability of physician-indicated targeted treatment.

Establishing a diagnosis for CI requires a comprehensive approach and an overall assessment of the patient’s cognitive performance using multiple diagnostic tools and is strictly the physician’s responsibility (21). Brief screening tests such as the Mini-Mental State Examination (MMSE) (22), the Clock Drawing Test (CDT) (23), and the Montreal Cognitive Assessment (MoCA) are used for an indicative examination of cognitive abilities. The MoCA test is a gold standard, one of the most commonly used cognitive screening tools worldwide. It is characterized by a high sensitivity and specificity for MCI (21), and short and standard versions of the MoCA appear to be effective in identifying CI (24). It was translated into many languages, including Slovak (25, 26). Its time-saving short version for pharmacy practice is suitable (27–29). If poorer cognitive abilities are noted in an orientation cognitive screening within pharmaceutical care, it does not mean the patient suffers from CI. A suspected CI is suggested. A physician’s assessment of the patient’s cognitive status is needed to confirm the CI (21).

### CI risk factors

1.2

The development of CI and dementia is related to the interaction of many factors. Nowadays, potentially modifiable factors are well-known (12) (Figure 1). Cardiovascular risk factors are together with Aging and the Incidence of Dementia (CAIDE) expressed by the CAIDE Dementia Risk Score (30). They can evaluate a patient’s risk of developing dementia (31). Most of these factors of CI, such as hypertension, obesity, diabetes and high cholesterol, can be effectively influenced by pharmacists’ interventions. At present, pharmacists’ competencies are expanding and include the management of chronic diseases and medication safety (32), assessment of potentially inappropriate medication use in the older adult (33), monitoring biochemical parameters, blood pressure measurement, obesity management, smoking cessation and others, all of which contribute to the individualisation of pharmaceutical care that is more patient-centered (34). Chronic cardiovascular disease and metabolic syndrome (MetS) are among the modifiable risk factors for dementia. Therefore, attention should be paid to monitoring cognitive abilities in patients suffering from these conditions. CI may lead to non-adherence to treatment, which in turn may result in the development of dementia (20, 35). Advanced pharmaceutical care now routinely includes the management of most modifiable risk factors for CI and dementia. This is a relevant basis for the subsequent expansion of pharmaceutical care targeting early recognition of CI through simple cognitive screening as a pharmaceutical service.

**Figure 1 fig1:**
[figure not shown]
Modifiable risk factors for dementia and the potential role of pharmacists in their management. Dark purple indicates routinely performed pharmaceutical interventions with a well-documented patient outcome. Light purple shows interventions with poor outcome evidence, and the black letters indicate risk factors outside the pharmacist’s competence. Figure was adapted from the original figure by Livingston et al. (12) with permission from Elsevier LTD., which has been expanded to include information regarding the potential role of pharmacists in their management according to Macekova et al. (34), using Inkscape graphics editor.

### Role of pharmacists

1.3

Pharmacists can support the management of most patients suffering from diseases that do not require a visit to the doctor, thus reducing the burden of medical care. Consequently, physicians can focus on patients with severe disorders (36). In addition, pharmacists can play a role in managing patients suffering from chronic diseases (37), including cognitive disorders (6, 8, 9, 38). Nevertheless, it is still uncertain whether these pharmaceutical interventions bring adequate benefits to the patients and improve their health status. The patient’s cognitive state may be the limitation for achieving satisfactory results, as in the case of CI, the patient needs an individual, specific approach in the provision of health care, including pharmaceutical care. For this reason, our study aimed to develop a standard protocol for assessing cognitive screening of patients aged 50 years and over in community pharmacies so that the pharmacist can adapt this approach to the patient in the provision of pharmacy care.

## Methods and analysis

2

### Design and setting

2.1

We designed a study protocol for a prospective observational clinical cohort study in Slovakia to evaluate multifactorial and specific risk factors for CI in the adult population aged 50+ as a part of advanced pharmaceutical care in community pharmacies (Figure 2). The current study protocol is developed based on our previous findings (39, 40) and offers an advanced method of identifying patients at risk for CI by pharmacist intervention. Firstly, we focus on performing a cognitive screening using a short version of the Montreal Cognitive Assessment (21, 28). Secondly, we will assess the risk of developing dementia according to the CAIDE Dementia Risk Score, which includes lifestyle factors, age, and comorbidities altogether expressed as the CAIDE score (31). Third, we will assess the risk of medication use by impacting cognitive health according to the ACB scale using the free available online ACB calculator (41).

**Figure 2 fig2:**
[figure not shown]
Flowchart of the study. CAIDE, Cardiovascular Risk Factors, Aging, and Incidence of Dementia (The CAIDE Dementia Risk Score), s-MoCA, short version of the Montreal Cognitive Assessment Screening Tool; ACB, Anticholinergic Burden Scale.

### Cohort and sample size calculation

2.2

Adult patients aged 50 years or older receiving pharmaceutical care (patients who visit community pharmacy for different reasons, e.g., to collect a medication with/without prescription, pharmaceutical counseling, etc.) in community pharmacies in Slovakia who can complete the questionnaires and are willing to participate in the study will be included. Inclusion and exclusion criteria are shown in Table 1. Exclusion criteria also include disorders which can be related to cognitive dysfunction (e.g., schizophrenia). Pharmacy clients will receive written information about the study objectives, and consent will be obtained to confirm participation. By their signature, they will also agree to participate only once (to avoid duplicities). Individuals will be informed that participation is voluntary and can be terminated at any time. Also, they will be ensured that access to the collected data will be restricted to the study investigators only. The minimum sample size for our analysis was based on the estimated proportion. The sample size was set using an online sample size calculator for a 95% confidence interval and a 5% margin of error (42), according to previously used in Kosirova et al. (33). The minimum number of included subjects was estimated to be 385 according to the total number of adults aged 50 and over in 2023 (*N* = 2,033,555); (43).

**Table 1 tab1:** Inclusion and exclusion criteria.

Inclusion criteria	Exclusion criteria
Adults aged 50 and older, patients with type 2 diabetes mellitus without age limitation Undergoing at least one counseling by a pharmacist No previous diagnosis of CI/dementia as determined by ICD-10 codes or the presence of a prescription for anti-dementia medications (cholinesterase inhibitors or memantine) Ability to consent to participate in the study Ability to communicate in Slovak	Adults outside the age criteria Adults in permanent senior care or nursing home A serious mental illness such as schizophrenia code ICD-10 and targeting medication A pre-existing diagnosis of CI/dementia

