## Outcomes

3

In this study, we focus on a cohort of adults aged 50+ with lower cognitive abilities expressed by s-MoCA scores (≤ 12 points). These patients will be defined as those with suspected CI (CI+) who will be referred for medical examination. We will then record whether a physician has confirmed our suspicion of CI.

In the CI+ group, we will collect data on the prevalence of CI risk factors (expressed by CAIDE score) and the use of risk medications (expressed by ACB score) and then compare them with a control group.

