## Statistical analyses and mitigation of bias

4

The obtained data will be analyzed using GraphPad, version 8.0.1 (GraphPad Prism, San Diego, CA, USA) and the SAS Education Analytical Suite for Microsoft Windows, version 9.3 (SAS Institute Inc., Cary, NC, USA). We will perform fundamental descriptive analyses (calculation of mean and SD), normality tests for the included variables, correlation tests, *t*-tests for two independent variables, and one-way analysis of variance (ANOVA) in the case of more independent groups. Multivariate regression models will be used to compare cognitive outcomes across subgroups.

Since there is no randomization or intervention control in this study, several types of bias can affect validity. In the study, we will mitigate selection bias through design-stage (broad and inclusive recruitment, clear criteria, consistent enrolment) and analysis-stage strategies (statistical adjustment, sensitivity analyses). Observer bias will be mitigated through standardization, pharmacist training, objective measurements, and data monitoring strategies. Social desirability bias will be mitigated through use of questionnaire design (e.g., using neutral wording and validated scales) and through pharmacist training with a focus on his/her empathy and neutrality.

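### The 5-point margin behind the sample size of 385 holds for one whole-sample proportion under simple random sampling at p = 0.5; it allows nothing for recruitment within pharmacies and does not carry over to physician confirmation among CI+ patients

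*Protocol article*

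**What the plan says.** Section 2.2 sets the size on one quantity: "The minimum sample size for our analysis was based on the estimated proportion". Neither that proportion nor its expected value is named. The section continues: "The sample size was set using an online sample size calculator for a 95% confidence interval and a 5% margin of error". The result is tied to a national head count: "The minimum number of included subjects was estimated to be 385 according to the total number of adults aged 50 and over in 2023", given there as 2,033,555.

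The abstract describes the sampling: "The study is a multicentric study that will include cognitive screening within pharmaceutical care". Under sections 2.2 to 2.4, willing pharmacy visitors are enrolled, and trained pharmacists (or students they supervise) collect the data and administer the test on site. The number of pharmacies, the number of patients per pharmacy and the intra-pharmacy correlation are not given.

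Section 3 defines CI+ as an s-MoCA score of 12 or less and has these patients referred. It adds: "We will then record whether a physician has confirmed our suspicion of CI". It also plans to describe CAIDE and ACB scores in CI+ and compare them with a control group. No expected CI+ share is given.

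Section 4 lists, for group comparisons, Student's t "tests for two independent variables, and one-way analysis of variance (ANOVA) in the case of more independent groups". It also mentions multivariate regression, statistical adjustment and sensitivity analyses. No pharmacy term is named.

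**The concern.** A reader will take 5 points as the precision of the study. Two features of the design stand in the way.

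First, people tested in one pharmacy share a catchment area, a recruitment style and often a tester. Section 5.2 itself says that conduct and evaluation of the screening depend on the pharmacist's experience and judgment. Results within a pharmacy are therefore likely to be correlated, and 385 such people carry less information than 385 independent ones. If the comparisons in section 4 ignore this, their standard errors will tend to be too small.

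Second, physician confirmation is observed only in CI+ patients, who are a part of the 385, and only where the follow-up contact of section 2.10 succeeds. That rate bears directly on the first hypothesis in section 5.1.2, so a reader needs to know how precisely it will be estimated.

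**Working it through.** **Inputs from the protocol.** Confidence 95% (z = 1.96), margin d = 0.05, population N = 2,033,555, minimum n = 385 (all section 2.2).

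**Inputs that are assumptions.** p = 0.5 (implied by the result, not stated); patients per pharmacy m = 5 to 20; intra-pharmacy correlation (ICC) 0.01 to 0.10; CI+ share 20% to 40%; follow-up response 60%. The document gives none of these.

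**1. Reproducing 385.**

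- n0 = z² p(1−p)/d² = 1.96² × 0.25 / 0.05² = 384.16
- Finite population correction: 384.16 / (1 + 383.16/2,033,555) = 384.09
- Both round up to 385, so the stated figure is right. The population size has almost no effect on it.
- Margin at n = 385: 1.96 × √(0.25/385) = 4.99 points

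The slack is less than one participant: 385/384.16 = 1.002. At p = 0.5, a design effect above 1.002 already takes the margin past 5 points.

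**2. Clustering by pharmacy, p = 0.5.** Design effect DE = 1 + (m − 1) × ICC; effective n = 385/DE; margin = 1.96 × √(0.25 × DE/385).

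| m | ICC | DE | Effective n | Margin (points) |
|---|---|---|---|---|
| 5 | 0.01 | 1.04 | 370 | 5.1 |
| 10 | 0.05 | 1.45 | 266 | 6.0 |
| 20 | 0.05 | 1.95 | 197 | 7.0 |
| 20 | 0.10 | 2.90 | 133 | 8.5 |

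**3. How much clustering a less extreme case absorbs.** The largest design effect that keeps 5 points is 385 × 0.05² / (1.96² × p(1−p)).

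- p = 0.3: 0.9625 / (3.8416 × 0.21) = 1.19; unclustered margin 4.6 points
- p = 0.2: 0.9625 / (3.8416 × 0.16) = 1.57; unclustered margin 4.0 points

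For a whole-sample proportion near 0.2, the second row of the table (DE 1.45) still gives 4.8 points; the fourth (DE 2.90) gives 6.8.

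**4. Physician confirmation within CI+, before any clustering.** Margin = 1.96 × √(p(1−p)/n), with n = 385 × share × response.

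| CI+ share | n, all followed | Margin, p = 0.5 | Margin, p = 0.2 | n at 60% response | Margin, p = 0.5 |
|---|---|---|---|---|---|
| 20% | 77 | 11.2 | 8.9 | 46 | 14.4 |
| 30% | about 116 | 9.1 | 7.3 | – | – |
| 40% | 154 | 7.9 | 6.3 | 92 | 10.2 |

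This step needs no assumption about correlation. Even at a CI+ share of 50% the margin at p = 0.5 would be 7.1 points.

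**The case against.** Several points on the other side are sound.

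- The sample size contains no arithmetic error, and 385 is a minimum, so more may be enrolled. A reader might infer from the clustering argument that 385 was miscalculated; it was not.
- Section 2.2 sizes one unnamed proportion. A reader might infer that the protocol promises 5 points for results within CI+ and breaks that promise. It makes no such promise; it only leaves open which quantity the margin covers.
- A reader might also infer that the outcomes in general are proportions within CI+. Only physician confirmation plainly is. CAIDE and ACB are expressed as scores and compared with a control group, the CAIDE objective in section 5.1.1 concerns the whole sample, and no outcome is labelled primary.
- p = 0.5 is the worst case. For a whole-sample proportion of 0.2 to 0.3, moderate clustering may leave the margin within 5 points, so it cannot be said flatly that the precision will be missed.
- The size of the clustering effect is unknown. Over the assumed range the design effect runs from negligible (1.04) to large (2.9).
- A smaller CI+ denominator does not make an interval invalid. An interval computed on the actual CI+ count is properly wide. Understated uncertainty comes from ignoring clustering, not from the subset.
- A pharmacy effect could sit in the regression or adjustment of section 4, and its details may be left to an analysis plan not shown.

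All of this narrows the point without removing it. The margin is stated in this document, and it rests on independence and on the full denominator. The design does not secure independence, and physician confirmation does not have the full denominator.

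**Conclusion.** The concern holds in limited form. The 5-point margin is right for one whole-sample proportion under simple random sampling at p = 0.5, and for little beyond that. At p = 0.5 practically any positive intra-pharmacy correlation exceeds it: 5.1 to 8.5 points over ICC 0.01 to 0.10 and 5 to 20 patients per pharmacy. At p = 0.3 or 0.2 it survives up to a design effect of about 1.19 or 1.57.

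For physician confirmation among CI+, the expected margin at p = 0.5 is about 11.2 to 7.9 points at CI+ shares of 20% to 40%, and 14.4 to 10.2 points at 60% response.

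The loss of precision in the subset follows from sections 2.2 and 3 alone. The clustering effect is likely in direction but cannot be fixed in size. The ICC, cluster size, CI+ share and response rate are all assumptions. This should be corrected, but it does not call for a larger sample.

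**What to change.** 1. Keep 385. In section 2.2, name the proportion that was sized, most naturally the overall CI+ proportion among pharmacy attenders who meet the recruitment criteria, and state the assumed p.
2. Restate its margin as about 5 points without clustering, with a range over plausible design effects as in the table above.
3. State separately the expected, wider margin for physician confirmation, with the assumed CI+ share and follow-up response.
4. Record a pharmacy identifier on each participant's form. Section 2.4 has each enrolled pharmacist supply the pharmacy's name and address, but Table 2, presented as the full list of recorded items, has no such field.
5. In section 4, account for pharmacy in the inferential comparisons through a random intercept or cluster-robust standard errors. For confirmation, use cluster-robust intervals rather than a mixed logistic model: some 46 to 92 responders (on the assumptions above) spread over pharmacies may not support a stable mixed fit.

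**Cost.** One extra field on the form, some rewording, a less favourable stated margin and somewhat wider intervals. No extra enrolment is needed.

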### Data collection

2.3

Data will be collected by trained pharmacists working in community pharmacies. They will be recorded on a pre-printed study form (socio-demographic data, lifestyle habits, evidence of comorbidities, and family history of Alzheimer’s disease and dementia). Table 2 summarizes all items that will be recorded.

**Table 2 tab2:** Basic characteristics and risk factors of the study population.

Socio-demographic features and lifestyle habits	
Age	Number of years
Gender	Multiple choice (*Female/Male*)
Education level	Number of school years
Waist circumference	Number (*cm*)
Physical activity habits	Open-ended questions (*frequency, duration per week, type of physical activity*)
Marital status	Multiple choice (*single/married/widow/divorced*)
Live in the household	Multiple choice (*alone/with other family members*)
Sleep duration	Open-ended questions (*frequency and duration per night/day*)
Smoking habits	Number of cigarettes per day
Alcohol consumption	Number and type of drinks per day
Comorbidities	
Hypertension	Yes/No
Dyslipidaemia	Yes/No
Type 2 diabetes	Yes/No
Overcome diseases	
Stroke	Yes/No
Thrombosis	Yes/No
Head injury	Yes/No
Actual and/or past problems	
Memory problems	Yes/No
Vision problems	Yes/No
Hearing problems	Yes/No
Smell problems	Yes/No
Family history of Alzheimer’s disease and/or dementia pathology (in line of parents, grandparents)	Yes/No

